### **EEG data (polysomnography)**

Awake EEG data will be processed with ELAN tools developed in the Brain Dynamics and Cognition laboratory (Aguera et al. 2011, <http://elan.lyon.inserm.fr>), as well as using SPM12 software (Wellcome Department of Cognitive Neurology, London, UK; <http://www.fil.ion.ucl.ac.uk/spm>). Spectral analysis of the continuous EEG signal will be done using time-frequency analysis programs developed in the team. Muscle artifact rejection will be done using the EEGLab program (Makeig and Delorme 2004; <http://sccn.ucsd.edu/eeglab/>).

Sleep EEG data will be analyzed by a sleep neurologist according to international criteria (Berry et al., 2014). Total sleep time, sleep latency, sleep efficiency, number and duration of nocturnal awakenings, and time spent in each sleep stage will be determined. More detailed analyses of the recordings will also be carried out by means of spectral analyses, which make it possible to highlight modifications of the cerebral activity in certain frequency bands. We will also calculate the density of different oscillations (slow waves, sleep spindles, ...) known to be involved in the process of memory consolidation during sleep and sensitive to the effects of age and Alzheimer's disease.

For the pre-processing of all brain imaging data (MRI and PET), the investigators have the possibility to use new software (or updates of the aforementioned softwares) developed before the pre-processing and data analysis phase in order to guarantee an optimal use of the imaging data.

The data obtained with the Somno-Art® device will be analyzed by the company PPRS, which developed the device and the processing algorithms. The algorithms will collect the following information for each night: total sleep time, sleep efficiency, sleep latency, WASO (wake after sleep onset), quantities of the different sleep stages, number of cycles, number of awakenings, number of transitions between stages and sleep instability index.

### 10.6.3. Verification of imaging data

The quality of the imaging data will be routinely assessed, in the days following acquisition, according to standard laboratory procedures. Each image is first checked visually by an investigator with expertise in this imaging modality. Specific procedures are also implemented for specific modalities:

- **fMRI:** the verification of movements and susceptibility artifacts will be performed both by visual analysis and via dedicated toolboxes such as the "TSDiffana" tool (<http://imaging.mrc-cbu.cam.ac.uk/imaging/DataDiagnostics>).
- **PET Scan:** the dose of product injected and the acquisition time window (0-10 min post-injection and 50-60 min post-injection for PET-Amyvid® early-frame and PET-Amyvid® late-frame respectively; 50-60 min post-injection for 18F-FDG PET) will be checked.

Finally, a procedure integrated into the SPM software will make it possible to detect, once the data have been pre-processed, extreme data ("outliers", likely to be defective data due to an anomaly during acquisition or processing) via the software *check sample homogeneity* (<http://www.neuro.uni-jena.de/vbm/check-sample-homogeneity/> ).

## 10.7. *Management and archiving conditions of the trial documents*

Trial documents will be archived during and after the trial at the Cyceron Center in a locked filing cabinet.

## 11. STATISTICAL ANALYSIS OF DATA

### 11.1. *Responsibility for statistical analysis*

The statistical analysis of the main objectives will be performed by the EUCLID statistician (EUropean CLInical trials platform and Development, CHU Bordeaux and Inserm, F-CRIN).

The statistical analysis of the secondary objectives, including the neuroimaging data, will be carried out within the work packages dedicated to the evaluation of the different objectives, as follows:

- Objective 2: WP 1 to 6;
- Objective 3: WP 1 to 6;;
- Objective 4: WP 1 to 6;
- Objective 5: WP 1;
- Objective 6: WP 2 to 6;
- Objective 7: WP 6
- Objective 8: WP 6
- Objective 9: WP 1 to 6.

The EUCLID statistician will be involved in the definition of the secondary statistical analyses and will be able to assist the WPs in their realization .

### 11.2. *Calculation of the study size*

#### Study on non-expert seniors:

The comparison between the meditation group and the no-intervention group is going to focus on the difference in 1) volume and 2) perfusion of the anterior cingulate cortex 18 months after the start of the intervention compared to the value at inclusion, with an expected effect size of 0.75 (effect size of short-term meditation vs. no intervention, from a meta-analysis on the effects of meditation on brain imaging markers: Fox et al, 2014). Given that the intervention in the current protocol is 18 months, we consider that the effect size will be at least equal to 0.75.

The same effect size of 0.75 is expected for the comparison between the meditation group and the English learning group on the difference in 1) insula volume and 2) insula perfusion 18 months after the start of the intervention compared with the inclusion value.

To show an effect size of 0.75 for each comparison, with 80% power and a two-sided first-species risk of 1.25% (Bonferroni correction because four comparisons will be performed) 42 participants per group must be recruited for a total of 126 participants.

Assuming that the effect size assumptions are conservative and that precautions are taken at the time of recruitment to best ensure adherence of participants to the trial, we expect that the risk of dropout after knowledge of the randomization group is very low and that the power of the study is preserved. However, we will implement close monitoring of these refusals at the beginning of the trial. In order to increase the statistical power of the secondary analysis on the FDG-PET examination carried out from

the second wave of inclusion, 24 participants will be recruited in addition, i.e. 8 additional participants per group (meditation, English, passive control) for a total of 150 participants.

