## **6.6. Visit no.1 – Inclusion visit**

The inclusion visit will take place in the investigating center in Caen, shortly after the participant's selection visit (less than 1 month delay). It includes different MRI sessions (anatomical and functional), two PET scans (Amyvid® and F-FDG), a blood sample, a detailed neuropsychological evaluation and a polysomnographic examination on awakening and during a night of sleep (see Figure 5 above).

The inclusion of expert meditating participants will be done "as it happens". On the other hand, the inclusion of non-expert seniors will be carried out in three waves (42 participants for wave 1 and 54 participants for waves 2 and 3). This organization in waves is linked to i) the logistical organization of the different appointments of the inclusion visit and ii) the logistics of the intervention periods (e.g. courses in groups, of reasonable size).

For each of these appointments, the participant will be taken care of by one of the investigators. As far as possible, this will be the same person for all the examinations. This person, called the "referent", will be responsible for organizing the various appointments for this visit and for following up with the participant on the site (welcoming and accompanying the participant on each visit). The neuropsychological tests can be done by the referent or by an investigating neuropsychologist. All the examinations will be carried out according to a standardized procedure (pre-established procedure in the course of the imaging and biological examinations and standardization of the instructions of the various tests proposed in functional MRI or during the neuropsychological evaluation).

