## **6.7. Randomization (Non-expert seniors only)**

Once all inclusion visit examinations have been completed for the entire wave (i.e., 42 participants for Wave 1 and 54 participants for Waves 2 and 3), participants will be contacted by telephone by one of the protocol investigators to confirm the planned start date of the intervention (Visit 2) within the next 2 weeks and to ensure that the participant still wants to participate in the trial prior to randomization. If the participant confirms their attendance, then the investigator can proceed to the randomization of the participant. To do so, they log into the e-CRF, complete the "randomization" page with the eligibility criteria and validate the content. The site immediately displays the group allocated to this participant.

If unable to connect to the e-CRF, the investigator will contact the Euclid platform.

The result of this randomization will be communicated to all participants in the same session at the same time shortly before the start of the intervention in order to limit the risk of participants dropping out if they were not assigned to the group they wanted (although this risk should be limited as early as the participant selection phase). Information will be communicated both by telephone and by mail (including important information about the first sessions of the intervention programs for participants assigned to the meditation and foreign language learning groups).

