## **10.1.2. Data collected during the inclusion visit (V1)**

### **10.1.2.1.1. MRI**

#### **Anatomical MRI:**

Six types of anatomical images of different weights will be acquired from all participants during the first MRI session, all in electronic format (images):

- A high spatial resolution T1 acquisition
- A targeted acquisition on the hippocampus
- A T2 acquisition
- A FLAIR acquisition
- A DKI acquisition
- A QSM acquisition
- An ASL acquisition (for participants in the 3rd wave of recruitment)

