## Sample size

### **For the randomized clinical trial with non-expert seniors:**

The comparison of the meditation vs. no intervention arms will focus on the change in 1) volume and 2) metabolism of the anterior cingulate cortex from baseline to the end of the 18-months intervention, with an expected effect size of 0.75.

We expect the same effect size of 0.75 for the comparison between the meditation arm and learning of English arm on the change in 1) volume and 2) metabolism of the insula from baseline to the end of the 18-months intervention.

To demonstrate an effect size of 0.75 for each of the four comparisons, with 80% power and a two-sided type I error of 1.25% (Bonferroni correction for test multiplicity), 42 participants per arm need to be included for a total of 126 participants.

In order to increase the statistical power of the secondary analysis on the PET-FDG examination carried out starting from the second wave of inclusion, 24 additional participants will be recruited (additional 8 participants per group) for a total of 150 participants.

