### Analysis strategy

#### Definition of analysis populations

The statistical analyses for the main objectives (primary endpoints) are described in the corresponding document.

For the secondary objectives (secondary endpoints) two types of analyses will be performed:

Analyses will be performed in intent to treat. All randomized participant will be included in the analysis in the group to which they were initially randomized and all their data is used, regardless of protocol deviations during the trial. Any missing value (missing= failure) will be replaced by the value corresponding to failure.

In order to assess the robustness of the results, a sensitivity analysis for the missing data will be performed using the maximum bias strategy using values reflecting failure and success (minimum and maximum difference, respectively) estimated on the observed data of all groups.

In addition, "per protocol" analyses will be performed: Participants' data will be analyzed in the group according to the treatment they actually received. Per protocol population includes "participants who attended at least 20% of intervention classes, or neither meditation nor foreign language training for participants in the passive control group.

For exploratory analyses not related with the intervention (e.g. analyses on baseline data independent from intervention group), all participants will be included in the analyses.

Decisions about which of these analysis strategies should be used will depend on the specific analyses and decided by the PI and validated by the ExCom.

Only participants presenting at least one of the following conditions can be excluded from the analysis:

- participants wrongly included with an unsigned consent;
- participants wrongly included for major non respected eligibility criteria;
- participants who withdrew their informed consent.

Decisions about exclusion will be made by the Trial Scientific Committee after documentation of observations by the EUCLID platform, blinded to the strategy group and to the participants' evolution after enrolment.

Except for these exclusions, the participants who died or who were lost to follow-up, or who interrupted the intervention or who left the study will all be included in the analysis.

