### Conventions for handling missing data

The following values are used in the database to describe the missing data:

- « NK » or « K »: Unknown
- « ND » or « D »: Not done
- « NA » or « A »: Not applicable

There will be no distinction in the statistical analyses according to the type of missing data.

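### Read literally, the secondary SAP's missing = failure rule would count wave-1 participants, who on the sample-size text have no inclusion FDG-PET scan, as failures in FDG change comparisons

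*Combined protocol and SAP*

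**What the plan says.** **When FDG-PET starts.** Protocol section 11.2 refers to the "secondary analysis on the FDG-PET examination carried out from" the second wave. The secondary SAP, under Sample size, agrees: "PET-FDG examination carried out starting from the second wave of inclusion, 24 additional participants will be recruited", 8 per group, for a total of 150. Protocol section 6.6 gives the wave sizes as "42 participants for wave 1 and 54 participants for waves 2 and 3".

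**How missing values are handled.** The secondary SAP (Definition of analysis populations) analyses every randomised participant in the allocated group and adds: "Any missing value (missing= failure) will be replaced by the value corresponding to failure". Its conventions for missing data list not-applicable as one of three missing codes and then state: "There will be no distinction in the statistical analyses according to the type of missing data".

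**Where choice is left.** The same section on analysis populations says that the strategy depends on the specific analysis, is decided by the principal investigator and is validated by the executive committee. The next section defines an available-data strategy but assigns it to no endpoint.

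**Where FDG is analysed.** Objective 2 in the secondary SAP compares the change from inclusion to 18 months in imaging measures between the three groups. Objective 8 compares FDG with early Amyvid, including their sensitivity to the interventions. Protocol section 10.6.2 provides for both voxel-wise and region-of-interest FDG analyses.

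**The concern.** A change from inclusion needs an inclusion scan. If FDG-PET began with wave 2, the change is absent for all of wave 1 by design, which tells us nothing about how those participants fared. The SAP has no category for this. Not-applicable is a missing code, all missing codes are treated alike, and a missing value becomes a failure.

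The authors did write an exception for the behavioural composite scores, where participants with missing scales are left out. They wrote none for FDG. The secondary per-protocol set does not close the gap either: unlike the per-protocol set in the primary SAP, it does not require the endpoint to be available.

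The trial was enlarged from 126 to 150 specifically to gain power for FDG. An imputation rule that fills more than a quarter of each arm with one extreme value works directly against that purpose.

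**Working it through.** **Plan's own figure.** A two-sample t test with d = 0.75, two-sided alpha 1.25% and 42 per arm has power 0.809 (41 per arm gives 0.797). The stated 42 per group is reproduced. The documents give no power figure for FDG, so the rest is a derived consequence.

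**Inputs from the documents**
- Waves: 42 + 54 + 54 = 150. Wave 1 is 42/150 = 28%.
- Allocation 1:1:1 (protocol section 3.2): 42/3 = 14 wave-1 participants and 108/3 = 36 wave 2–3 participants per arm.
- Alpha: two-sided 5% for other secondary endpoints (secondary SAP, Type I error rate).

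**Assumptions**
- FDG effect of 0.75 SD, borrowed from the primary endpoints, with 0.50 SD as a second case.
- Normal change scores with SD 1; no dropout among those scanned; exactly 14 wave-1 participants per arm.
- Failure is the lowest change observed over the three arms. Primary SAP section 3.6.1 defines it so. The secondary SAP spells out minimum and maximum only for its sensitivity analysis.

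**Available data only (noncentral t)**
- 36 per arm: power 0.88 at d = 0.75 and 0.55 at d = 0.50.
- Without the 24 extra participants there would be 36 − 8 = 28 per arm: 0.79 and 0.45.

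**Wave 1 imputed as failure, d = 0.75**
1. Both arms receive the same constant for 14 of 50 values, so the mean difference is (36/50) × 0.75 = 0.54, a factor of 0.72.
2. In simulation the pooled minimum averages −2.41. The within-arm variance is 0.72 + 0.72 × 0.28 × (arm mean − minimum)². Controls: 0.72 + 0.2016 × 2.41² = 1.89. Meditation: 0.72 + 0.2016 × 3.16² = 2.73. The pooled SD is √2.31 = 1.52.
3. The standardised effect becomes 0.54/1.52 = 0.355.
4. The test's standard error is 1.52 × √(2/50) = 0.304, so significance needs a difference of 1.984 × 0.304 = 0.603.
5. The difference itself varies only through the scanned values: SD 0.72 × √(2/36) = 0.170.
6. Power is about P[Z > (0.603 − 0.54)/0.170] = P(Z > 0.37) = 0.35.

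**Simulation** (normal data, minimum over three arms)

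| True effect | t, available data | t, imputed | Wilcoxon, imputed |
|---|---|---|---|
| 0.75 | 0.88 | about 0.35 | about 0.42 |
| 0.50 | 0.55 | about 0.09 | about 0.12 |
| 0 | 0.05 | 0.001–0.002 | 0.001–0.002 |

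**Maximum-bias analysis.** Setting 28% of each arm to opposite extremes moves the difference by 0.28 × the observed range. With a range of about 5 SD (normal assumption) that is about ±1.4 SD, nearly twice the assumed effect. The sensitivity analysis could not be informative.

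**The case against.** **The SAP does not force this result.** The investigator and executive committee may choose the strategy for each analysis, and an available-data strategy is defined. This stands: the literal reading is the default, not a certainty. But the listed intention-to-treat option carries missing = failure, and a change of 28% in the denominator should not wait for a later decision.

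**A reader might infer that wave 1 was never scanned with FDG.** The documents do not show that. The sample-size text implies only that there was no inclusion scan. Table 3 in protocol section 6.2 lists FDG at V1 for all seniors, section 6.10 lists two PET scans at V3, and the dosimetry table in section 14.1 includes FDG at V1, V3 and V4. None makes an exception for wave 1. These passages conflict with section 11.2 and must be reconciled.

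**Voxel-wise FDG maps cannot take a single failure value.** Correct. The rule can affect only region-of-interest change measures.

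**Objective 8 and ASL.** A reader might infer that the rule makes FDG look less sensitive than early Amyvid, or that ASL has the same problem to a larger extent. For Objective 8 the SAP plans comparisons and correlations without a defined test, so no distortion can be computed. Only its part on sensitivity to the interventions could be affected. For ASL, protocol section 10.1.2 lists "An ASL acquisition (for participants in the 3rd wave of recruitment", while the MRI2 description in section 6.6 has no such limit, and ASL is not named as an outcome. There is no defined endpoint on which to base a claim.

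**Conclusion.** The point holds for region-of-interest comparisons of FDG change, on a literal reading of the secondary SAP and on the sample-size text that FDG began with wave 2. Under the stated assumptions, power at an effect of 0.75 SD falls from 88% to about 35% (t) or 42% (Wilcoxon), and at 0.50 SD from 55% to about 9% (t). The estimated difference is 0.72 of the true one. At 0.75 SD the loss of roughly 50 percentage points far exceeds the gain of 9 from the added participants.

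The harm is attenuation and lost power. A reader might suspect spurious positive findings, but with wave 1 balanced across arms the null rejection rate drops to 0.1–0.2%.

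The FDG effect sizes, normality, complete follow-up of those scanned and the failure value are assumptions; the documents state no FDG effect or power. This is a secondary endpoint and the primary analysis is not affected. The correction should be made because a stated rule gives a wrong result here and the change is cheap.

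**What to change.** In the secondary SAP:
- State that FDG change endpoints are analysed in participants scheduled for the inclusion FDG scan. On the current sample-size text these are waves 2 and 3, planned at 36 per arm.
- Exclude values not scheduled by design from both missing = failure and maximum-bias imputation, and amend the sentence that treats all missing codes alike.
- Run any Objective 8 comparison of sensitivity to the interventions on the same participants for both tracers.
- Restore brain glucose uptake to the radiological outcome list. The protocol and the primary SAP include it; the secondary SAP does not.

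In the protocol, reconcile Table 3, section 6.10 and the dosimetry table in section 14.1 with section 11.2 on who has FDG-PET and when. Apply the same denominator rule to ASL only if ASL change is tested, after reconciling section 6.6 with section 10.1.2.

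The cost is a few sentences in the secondary SAP and a footnote to Table 3. No new data are needed.

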#### Study on the expert meditators:

Studies of expert meditators assessing meditation-related changes in brain activity have shown an effect size of  $d=0.74$  (calculated for fMRI change in the insula in response to emotional stimuli; Lutz et al., 2013).

For reasons of recruitment capacity, it was agreed to recruit 30 expert meditators into the trial.

The inclusion of 30 expert meditating participants will allow us to have a power of 95% for the comparison to the 126 non-expert participants, with a first species risk of 5%, to show an effect size of 0.74 in the comparison of brain imaging data.

For the comparison of the 30 expert participants to the 126 non-expert participants, we will have 90% power to show an effect size of 0.67 and 80% power to show an effect size of 0.58, with a two-sided first species risk of 5%.

### **11.3. *Description of the statistical analysis plan***

This protocol aims to determine the effects of a long-term meditative practice on biological and behavioral markers notably associated with aging and Alzheimer's disease (AD), and to better understand the cognitive and emotional mechanisms underlying these effects. To meet the main and secondary objectives (see part 2), a set of statistical analyses will be conducted.

The statistical analysis plan will be the subject of a complete and specific document separate from the protocol. The main elements are included in this chapter.

#### **11.3.1. Analysis strategy**

The main analysis will be carried out on an intention-to-treat basis, i.e. all randomized patients will be included in the analysis in the group in which they were initially randomized, and all their data will be used regardless of their changes in strategy during the research, with the "missing = failure" strategy, i.e. any missing value will be replaced in the analysis by the value corresponding to failure (minimum difference between 18 months after the intervention and inclusion), estimated on the data observed in all groups combined.

In order to assess the robustness of the results, a sensitivity analysis to missing data will be performed using the maximum bias strategy by using the values reflecting the failure and success (minimum and maximum difference respectively) estimated on the observed data for all groups combined.

A sensitivity analysis will also be performed by including only participants who attended at least 20% of the meditation sessions and exercises and who completed the examinations for the primary judgement criterion.

Some features may be strongly associated with volume and perfusion of the anterior cingulate cortex or insula. These characteristics could play a confounding role if, despite randomization, an imbalance was observed. Therefore, the comparative analysis of the primary judgemental criteria could be adjusted for potential confounders such as age, education, and gender. These adjustments may require the use of appropriate models, the relevance of which will be discussed according to the distribution and type of variables.

The description will always be done globally and by treatment group.

Tests for the primary criteria will be performed at the risk of error of the first kind  $\alpha = 1.25\%$ .

Tests for secondary criteria will be performed at the overall risk of error of the first kind  $\alpha = 5\%$ .

